### Endpoints

The primary endpoint is the 6-month global postoperative morbidity, i.e., the number of patients who develop at least one complication at the 6-month follow-up, encompassing both surgical and medical complications, as well as the morbidity of ileostomy closure. The 6-month timepoint is defined from the completion proctectomy and is therefore the same in both groups. We chose a 6-month endpoint because half of the patients will undergo ileostomy closure 6 to 12 weeks after IPAA. Therefore, a one-month or 3-month endpoint would be too short to correctly assess the morbidity of completion proctectomy +/− ileostomy closure. Moreover, a significant part of morbidity related to defunctioning ileostomy occurred in the long-term (i.e., after 30 days) in previously published studies [7, 8].

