The secondary endpoints are as follows: 6-month major morbidity based on the Clavien-Dindo classification, [14] i.e., number of patients who develop at least one major complication at the 6-month follow-up; 6-month unplanned reoperation rate, i.e., any unplanned abdominal surgery, whether urgent or elective, other than ileostomy closure; 6-month anastomotic leakage rate assessed by a CT scan with an iodine injection, i.e., pelvic abscess, pelvic extradigestive air, pelvic free fluid or pelvic infiltration; 6-month mortality (linked or not with the disease); initial and cumulative 6-month length of hospital stay; 6-month unplanned readmission rate, i.e., other than for ileostomy closure; global and digestive quality of life (QoL) assessed by the Cleveland Global Quality of Life (CGQL) score [15] and the EuroQol Five-levels (EQ-5D-5 L) (i.e., utility values for health states) [16] at baseline and 3 and 12 months from continuity restoration (i.e., either IPAA or ileostomy closure); functional results assessed by the Cleveland Pouch Functional score (PFS) 3 and 12 months from continuity restoration [15]; 12-month pouch results: pouch failure (i.e., with definite ileostomy), anastomotic stricture, pouch in place, and repeat IPAA 12 months from continuity restoration; 12-month global morbidity (i.e., the number of patients who develop at least one complication 12 months from continuity restoration); and 12-month cost-utility analysis, performed 12 months from continuity restoration (cf. *‘* Economic assessment’ below). Though many redo-IPAAs are performed after one year, it is a secondary endpoint and it was felt not relevant enough in this trial to extend its follow-up.

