#### Intervention

An anesthesia consultation is planned before the surgery according to the habits of each department. Participation in the study will not alter the anesthetic procedures. The technical modalities of IPAA are not restricted, but it is mandatory that these modalities are identical in both groups for each center in terms of the type of approach (laparoscopic, single-port, robotic), type of anastomosis (hand-sewn or stapled), pelvic drainage and pouch drainage. Open surgery can be the chosen surgical approach for some patients, provided that a mini-invasive approach cannot be performed due to the surgical history or medical contra-indications, as estimated by the surgeon in charge. A J-pouch will be mandatory as it is the pouch of reference [18].

The defunctioning ileostomy is a covering loop ileostomy, which can be fashioned either in the right or left iliac fossa. The use of an ostomy rod is not mandatory and left to the surgeon’s judgment. Ileostomy closure will be performed 6 to 12 weeks after IPAA as per local protocol or later in case of pelvic sepsis. During stoma closure, the type of ileo-ileal anastomosis (whether end-to-end or side-to-side, hand-sewn or stapled) is not restricted. A CT enema scan can be performed before ileostomy closure to assess the absence of anastomotic leakages, as per the local protocol.

The patients randomized in the experimental group will be treated by completion proctectomy and the creation of an IPAA without a defunctioning ileostomy, which corresponds to a modified two-stage IPAA. As defunctioning ileostomy is omitted in this group, an anastomotic leakage test can be performed when deemed necessary by the surgeon in charge. However, the anastomotic leakage test will not be mandatory.

No concomitant care and interventions are prohibited during the trial.

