#### Statistical analysis

A sample size calculation will be performed on the hypothesis formulated on the primary endpoint, i.e., the overall morbidity, assessed 6 months post-randomization. Based on previous reports, the overall 6-month morbidity rate is 30% in the case of no ileostomy creation (i.e., experimental group) vs. 55% otherwise (control group) [6–8, 11–13]. With the alpha risk and power fixed to 0.05 and 0.80, respectively, 88 patients need to be included in each group, or 176 in total [Power Analysis and Sample Size Software Version 2008, Utah, USA]. Considering a drop-out rate of 10%, the objective is set to 194 patients.

The full analysis population (including all subjects who will be randomized and will at least be evaluated at baseline) will be used in the primary analysis, and the per-protocol population (including all subjects who will be randomized and will not have major protocol deviations) will be used in the secondary analysis to assess the robustness of the results. The demographic and baseline characteristics will be summarized for the 2 groups (‘control’ and ‘experimental’ groups). The scores of the QoL questionnaires will be calculated from the algorithm provided by the authors of the tools. No comparisons will be provided in accordance with the CONSORT guidelines.

The primary endpoint will be compared between the 2 groups (χ^2^ test or Fisher’s exact test) for the primary analysis. Logistic regression will be performed to adjust for potential confounding factors; variables relevant to the models will be selected based on their clinical interest and/or a threshold *p*-value ≤0.1 during univariate analysis. The final models will express the odd ratios and their 95% confidence intervals. The unadjusted analysis will be the primary analysis, and the adjusted analysis will be a complementary analysis. For the secondary endpoints, quantitative data will be compared using the Student’s t test or Mann-Whitney U test in accordance with the variable distribution, whereas qualitative data will be compared using χ^2^test or Fisher’s exact test, as appropriate.

For the analysis of overall survival, the last date of known contact will be used for subjects who have not died (the subjects will be considered censored). Overall survival will be estimated according to the Kaplan-Meier method. Comparisons between the 2 groups will be performed with the log rank test for the Kaplan-Meier estimates. Cox models will be created.

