#### Economic assessment

As recommended by the French High Health Authority (HAS), the clinical endpoint used for the cost-utility analysis will be the QALYs (https://www.has-sante.fr/portail/jcms/r_1499251/en/choices-in-methods-for-economic-evaluation). Preference-based utility scores will be calculated using the EQ-5D-5 L questionnaire. The final result of the economic analysis is the incremental cost-utility ratio (ICUR), which expresses the additional costs per additional QALY. The perspective will be that of the society (HAS recommendation). A second analysis will be conducted from the healthcare provider perspective (i.e.*,* hospital). This analysis will take into account the difference between the costs and the tariffs paid for each cost category. The principal economic analysis will be conducted over the time horizon of the IDEAL trial, i.e., 12-month horizon to capture both the immediate and relevant consequences of both the ‘no ileostomy’ and ‘ileostomy’ strategies, which is a period during which all effectiveness and cost data will be precisely collected. To capture the long-term consequences of the intervention compared, we will extend the time horizon of the cost-utility analysis over the patients’ lifetime. The results of the modeling approach will contribute to the decision-making process by comparing our results with other economic analyses conducted in the field of inflammatory bowel disease and investigating long-term survival and costs.

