#### Data collection and monitoring

An electronic Case Report Form (eCRF) will collect the patients’ baseline data (sociodemographics, such as current age, age at UC diagnosis, sex, body mass index, weight gain since subtotal colectomy, ASA score, and smoking status; medical history, such as extent of UC, associated primary sclerosing cholangitis, and associated comorbidities; surgical history, such as indications for primary STC, delay between STC and IPAA, postoperative course of subtotal colectomy, and history of other surgical procedures; current and previous treatments, such as anti-TNF, immunosuppressive treatment, and corticosteroid therapy; and baseline QoL assessment, using CGQL and EQ-5D-5 L) as well as perioperative, short- and long-term data according to the abovementioned endpoints. Each patient will participate in the study for 15 months (as there are 12-month data collect points from continuity restoration, which is performed up to 3 months after IPAA in case of defunctioning ileostomy). Clinical reviews will be performed one and 6 months after IPAA and 3 and 12 months after continuity restoration (i.e., either IPAA or stoma closure).

Monitoring will be conducted to ensure that the data are accurate/complete, the safety and rights of subjects are being protected, and the study is conducted in accordance with the applicable regulatory requirements. No deidentified individual clinical trial participant-level data (IPD) will be shared. This monitoring (including data management and data quality insurance) will be ensured by the sponsor. The following monitoring will be conducted: informed consent, deviation of protocol, data collection, and safety and rights of participants. All the eCRFs will be routed to the coordinating center, APHM ([name]). Data entry will be performed using REDCap. Quality assurance will be performed from the final database (data manager). The database will be forward to the statistical team (Aix-Marseille Univ, APHM, Clinic Research Platform). The study information of this protocol has been posted on clinicaltrials.gov. The status of this trial is pending: the first inclusion is estimated for September 1st^,^ 2019.

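### 12-month morbidity, pouch failure and cost-utility are dated from continuity restoration, which comes 6 to 12 weeks or more later in the ileostomy arm, so the arms are not compared over the same period from surgery

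*Protocol article*

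**What the plan says.** All references are to the protocol article.

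- **Endpoints, secondary.** Quality of life is assessed at "3 and 12 months from continuity restoration (i.e., either IPAA or ileostomy closure"), which defines the term. The same clock governs 12-month global morbidity, defined as "the number of patients who develop at least one complication 12 months from continuity restoration", the 12-month pouch results (including pouch failure, meaning a definite ileostomy), and the economic endpoint: "12-month cost-utility analysis, performed 12 months from continuity restoration".
- **Intervention.** "Ileostomy closure will be performed 6 to 12 weeks after IPAA as per local protocol or later in case of pelvic sepsis".
- **Economic assessment.** The main analysis runs over the trial's own horizon, "i.e., 12-month horizon to capture both the immediate and relevant consequences" of both strategies. The section does not say when that horizon starts.
- **Data collection and monitoring.** Each patient takes part for 15 months, justified by restoration "which is performed up to 3 months after IPAA in case of defunctioning ileostomy". Reviews are planned at 1 and 6 months after IPAA and at 3 and 12 months after restoration.
- **Endpoints, primary.** Here the article chooses a common surgical origin and gives its reason: "The 6-month timepoint is defined from the completion proctectomy and is therefore the same in both groups". The Statistical analysis section, however, describes the same endpoint as "the overall morbidity, assessed 6 months post-randomization".

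**The concern.** Continuity restoration happens after randomisation, and its timing depends on the arm. In the no-ileostomy arm it coincides with the index operation. In the ileostomy arm it is a second operation, and its date can itself depend on outcome because pelvic sepsis delays it. An endpoint dated from it starts at a different point of the treatment pathway in each arm.

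This matters most for 12-month global morbidity and cost-utility. Both are meant to compare the whole consequences of the two strategies, including the stoma period and its closure. It also affects pouch failure, because a patient left with a permanent ileostomy may never reach the event that starts the clock. The article recognises the principle for its primary endpoint and departs from it for these endpoints. The reason it gives for choosing that common origin applies equally to them.

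**Working it through.** **Inputs from the article.** Closure is 6 to 12 weeks after IPAA, with no upper limit after pelvic sepsis (Intervention). Participation is 15 months, and restoration is taken to occur within 3 months (Data collection and monitoring). Recruitment lasts 33 months and the study 48 months (Methods and design). One month is 365.25 / 12 / 7 = 4.348 weeks.

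**Step 1: the article's own follow-up figure.** 12 months + 3 months to restoration = 15 months, as stated. 33 + 15 = 48 months, as stated. So the plan does place the final control assessment up to 15 months after surgery.

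**Step 2: time from surgery to the 12-month assessment.**

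| Arm | Restoration after IPAA | Assessment after IPAA | Relative to 12.0 |
|---|---|---|---|
| No ileostomy | 0 | 12.0 months | 1.000 |
| Ileostomy, closed at 6 weeks | 6 / 4.348 = 1.38 months | 13.38 months | 1.115 |
| Ileostomy, closed at 12 weeks | 12 / 4.348 = 2.76 months | 14.76 months | 1.230 |
| Ileostomy, closed later after sepsis | more than 2.76 months | more than 14.76 months | more than 1.230 |

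**Step 3: the two possible counting windows.** The article does not say whether events before closure count.

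- *From surgery to restoration + 12 months.* Controls have 11.5% to 23% more time at risk. As an illustration, assume the same constant hazard in both arms, so that risk(t) = 1 − (1 − p)^(t/12), where p is the risk at 12 months. Then p = 30% becomes 32.8% to 35.5% in controls, p = 40% becomes 43.4% to 46.7%, and p = 55% becomes 59.0% to 62.6%. These differences come from exposure time alone. The risks and the constant hazard are assumptions. Complications that cluster soon after surgery would make the late extra weeks count for less.
- *From restoration to restoration + 12 months.* The windows have equal length but different content. In the no-ileostomy arm the window starts at the proctectomy and takes in early leaks and the index stay. In the ileostomy arm it starts at closure and omits the proctectomy, early leaks, stoma complications and 6 to 12 weeks of cost.

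Neither window makes the arms comparable.

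**Step 4: patients with late or no closure.** If closure comes after 3 months, restoration + 12 months exceeds the 15 months of participation. A control whose stoma is never closed has no restoration date, so no 12-month date is defined.

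**Step 5: effect of a common origin.** With both arms dated from the completion proctectomy and read at 12 months, the gap of 1.38 to 2.76 months or more becomes 0. At that date control pouches will have been in use for 12 − 2.76 = 9.2 to 12 − 1.38 = 10.6 months.

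**The case against.** Several counter-arguments deserve weight.

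- **Only secondary endpoints are involved.** The primary endpoint is dated from the proctectomy, and the 6-month secondary endpoints are not tied to restoration. This stands and sets the severity.
- **The economic section fixes a 12-month horizon.** The restoration wording might mean only when the last data are collected. That is possible, but the section does not state a start. A 12-month window from surgery ends before the control arm's final assessment, and one from closure misses that arm's surgery and stoma period. The origin still has to be chosen.
- **The restoration clock has a rationale.** It compares pouches after equal time in use. This is sound for function scores, and reasonable as a supportive view of results such as stricture. It does not justify the clock for overall morbidity or costs.
- **A condensed article may leave counting rules to a fuller document.** True of details, but the origin is stated here, and it differs by arm.

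Three stronger readings are tempting and are not supported:

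- *That never-restored patients are dropped from the analysis.* The Study population section lists definite terminal ileostomy as an example under its exclusion criteria, which might suggest this. But nothing says such patients leave the analysis. The full analysis population keeps every randomised patient with a baseline evaluation, and definite ileostomy is itself the pouch-failure outcome. What they lack is a defined assessment date.
- *That the plan builds in a QALY artefact of known size and direction.* At assumed utilities of 0.7 to 0.9, 6 to 12 weeks (0.115 to 0.230 years) equals 0.08 to 0.21 QALY. That would be added to the control arm only if QALYs were summed from surgery over unequal periods, which conflicts with the stated 12-month horizon. Under the other window there is no extra control time.
- *That the randomised comparison is lost altogether.* All randomised patients remain, and the time origin can be repaired.

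**Conclusion.** The point holds for 12-month global morbidity, 12-month cost-utility and the dating of pouch failure. Their time origin depends on the arm. Either controls are observed for 13.4 to 14.8 months or more after surgery against 12.0, or their perioperative and stoma periods are left out while the experimental arm's perioperative period is included. The 11.5% to 23% excess follows directly from the planned closure interval. The morbidity percentages are illustrations that rest on an assumed risk and a constant, equal hazard.

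Patients never closed have no 12-month date, and those closed after 3 months fall outside planned participation. No claim is made about the size or sign of a QALY difference, or that patients are removed from analysis.

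This should be fixed, but it does not threaten the primary comparison: the primary endpoint and the sample size are unchanged. The two origins given for the primary endpoint are a minor related inconsistency. Randomisation is at least the day before surgery with no stated maximum, so the gap has no stated upper limit.

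**What to change.** 1. Date 12-month global morbidity, pouch failure, costs and QALYs from the completion proctectomy, with one common end date in both arms. Twelve months after IPAA lies within the 15 months already planned.
2. Count patients whose continuity has not been restored by that date as not having a functioning pouch.
3. Keep the restoration clock for pouch function scores and, as a supportive analysis, for pouch results that depend on time in use, such as stricture.
4. State the same origin and end date in the Economic assessment section.
5. Reconcile the Intervention section, which allows closure beyond 12 weeks after pelvic sepsis, with the 15-month participation, which rests on restoration within 3 months.
6. Replace the post-randomisation origin in the Statistical analysis section with the proctectomy origin already given for the primary endpoint.

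**Cost.** For morbidity, pouch failure and costs this is mainly wording, because events and costs can be dated and cut at a common point. Utilities need more. EQ-5D is scheduled only at baseline and at 3 and 12 months from restoration, which in controls is about 4.4 to 5.8 and 13.4 to 14.8 months after IPAA. Control-arm QALYs to 12 months therefore need interpolation. Adding EQ-5D at the existing 1- and 6-month reviews would strengthen this without new visits. The 1-month review precedes the planned closure window, so it would supply a value for the stoma period, for which none is specifically scheduled; the 12-month value in controls would still be interpolated. The remaining trade-off is that control pouches will have been in use 6 to 12 weeks less at the common date, which the supportive analysis in item 3 addresses.

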### Participating centers

The recruitment will be performed in 15 French public academic teaching hospitals. All participating sites will sign a convention with the Direction of Research and Clinical Innovation of APHM for ethical approval before beginning patient inclusion. All these centers are tertiary expert units in IBD, as it has been demonstrated that IPAA should be performed in mid- to high-volume centers, namely, those that perform at least 3 IPAA procedures per year [17].

### Study population

The inclusion and non-inclusion criteria are summarized in Table 1. Completion proctectomy can be indicated after any primary subtotal colectomy, irrespective of both the indication of subtotal colectomy and the time from the previous procedure. UC and IBDU are defined according to the third ECCO consensus guidelines [18]. The exclusion criteria are as follows: wishes to interrupt his/her participation during the study; and no benefits from IPAA (e.g., definite terminal ileostomy). An early stoma closure due to high output with electrolyte imbalances is not an exclusion criterion.

**Table 1 Tab1:** Inclusion and exclusion criteria

Inclusion criteria	Non-inclusion criteria
– Age ≥ 18 years; – UC or IBDU requiring completion proctectomy with IPAA and who can be treated by both strategies; – Affiliation with or benefitting from a social security system; – Freely signed written informed consent form.	– Indications for total proctocolectomy in a one-stage or traditional two-stage fashion – Crohn’s disease – Pelvic radiotherapy – Indications for total mesorectal excision – Vulnerable patient under the French laws (e.g., minors, pregnant/breastfeeding women) – Participation in another research protocol influencing the postoperative morbidity – No consent to participle, or unable to give a written consent.

The selection criteria are barely restrictive but must be followed to respect the current guidelines. Patients requiring a completion proctectomy after primary subtotal colectomy represent approximately 40% of all colonic IBD patients needing IPAA. It is therefore a frequent situation and restricting the inclusion criteria to completion proctectomy only rather than including all IPAA permits a more homogenous population. Moreover, one-stage IPAA is now restricted to very selected cases of IBD, as explained above in the rationale. The inclusion of patients who present with FAP was estimated to be not relevant, as they scarcely undergo completion proctectomy and do not have rectal inflammation. Select patients who present with colonic Crohn’s disease can undergo IPAA [19]. However, they are not the best candidates for completion proctectomy and IPAA without ileostomy, as they are exposed to a higher risk of pouch failure than UC patients [20]. Therefore, Crohn’s disease patients will not be included in the study.

### Ethics

The research carried out will be in accordance with the Helsinki declaration. This study was submitted to the national drug agency (ANSM) and to the ethics committee “CPP Sud-Est 3” on April 30th, 2019; it was approved after minor corrections. Prior to randomization, written informed consent will be obtained from all patients.

